### Randomization

After baseline data collection, all selected clusters were randomized into 2 arms. The principal investigator or data collectors did not know whether a particular cluster belonged to the control or intervention arm at baseline data collection, which minimized observer bias during this stage.

All selected clusters were arranged in ascending alphabetical order, and a number was assigned to each cluster. An online randomization sequence generator assigned the numbers 1 to 20 into 2 arms. The intervention arm had 10 numbers, and the control arm had 10 numbers. Clusters with allocated numbers were randomly assigned to the intervention and control arms.

### Allocation Concealment

The principal investigator enrolled the clusters in the study. The randomization sequence generation was delayed until baseline data collection was completed, ensuring that the principal investigator who enrolled the clusters was unaware of the randomization sequence at the time of enrollment.

The randomization sequence was generated by an independent researcher (not a research team member) from a different district. He was asked to allocate numbers from 1 to 20 into the intervention and control groups using a random sequence generator. He was unaware of the cluster list and the allocated number for each cluster. He did not know about the offices and their distribution in the Galle district as he was selected from a different district. This independent sequence generation randomized clusters into the intervention and control arms without manipulation.

### Intervention

#### Overview

The intervention was developed to match the SOC of the participants.

It has been highlighted that different SOCs require different processes of change to progress from one stage to another. Prochaska and Velicer [12] have described the relationship between SOCs and the processes of change that correspond to each one (Textbox 1).

Stages of change and the processes of change that correspond to each one.
**Precontemplation**
Consciousness raisingDramatic reliefEnvironmental re-evaluation
**Contemplation**
Consciousness raisingDramatic reliefEnvironmental re-evaluationSelf–re-evaluation
**Preparation**
Self- and social liberation
**Action**
Contingency managementHelping relationshipCounterconditioningStimulus control
**Maintenance**
Contingency managementHelping relationshipCounterconditioningStimulus control

According to Prochaska and Velicer [12], people in the precontemplation and contemplation stages need more consciousness raising, dramatic relief, self–re-evaluation, and environment re-evaluation. In these processes, they are provided with information on healthy and unhealthy behavior. Furthermore, the emotional and imaginary comparison of healthy and unhealthy behavior is facilitated. Similarly, the later stages, such as preparation, action, and maintenance, need processes of change such as self-liberation, contingency management, helping relationships, counterconditioning, and stimulus control. In these processes, more emphasis is placed on replacing the unhealthy behavior with a healthy one, monitoring whether the participant is on the correct path, and ensuring support from the environment [12].

Therefore, interventions to raise awareness and provide emotional arousal were designed for the precontemplation and contemplation stages. In contrast, interventions supporting and monitoring healthy behavior were designed for the preparation, action, and maintenance stages.

For precontemplators and contemplators, a 30-minute awareness-raising lecture was conducted at the beginning of each month during the intervention period of 3 months, and the following topics (one topic for each month) were discussed in each lecture in the order given (Multimedia Appendices 5-7): NCDs and their risk factors; risks of an unhealthy diet and benefits of a healthy diet, as well as strengths, weaknesses, opportunities, and threats analysis for behavior change; and how to change to a healthy diet.

While providing information to increase awareness, emotional arousal and self–re-evaluation were incorporated into all 3 lectures. The benefits of a healthy diet were highlighted, and participants were encouraged to contemplate the benefits of a healthy diet and the harmful effects of an unhealthy diet.

The lectures were delivered by a medical officer who was competent in public speaking and experienced in NCD prevention activities. The content of the lectures was discussed with the lecturer, and the objectives and methodology of the study were explained. It was emphasized to the lecturer to ensure similarity in the presentation and points highlighted in the lectures delivered to all intervention clusters. A slide show was prepared, and the lecturer and principal investigator agreed on the points to be discussed with each slide. A narrated lecture was circulated (through email or other electronic media) to the participants who were not able to take part in the lecture.

A separate intervention was designed for the preparation, action, and maintenance stages aiming to support and monitor the healthy behavior to be started or already started.

The intervention introduced a daily serving counter designed by the principal investigator based on serving recommendations published in the FBDG for Sri Lankans [4]. It allowed the participants to record their daily intake of servings of different food groups. The recommended servings were indicated for each food group. The lower and upper limits of recommended servings, where they are considered unhealthy, were indicated in red. A guide on serving sizes for each food group was added (Multimedia Appendix 8).

In addition, a mobile app with similar functions (the serving guide and the ability to record servings) was also developed for smartphone users.

#### Assessment of Adherence to the Intervention

Attendance at the in-person lectures was recorded. Feedback was obtained from those who were provided with the narrated lectures, asking them whether they watched the presentation. If no feedback was received within 5 days of receiving the narrated lecture, it was considered as nonparticipation in the lecture.

The principal investigator reviewed the marking of the serving counter monthly, visiting the office at the end of each month. Participants were informed of the date of the investigator’s visit and asked to bring the marked serving counters to be checked for completeness. If a participant missed more than 2 marking days per week during the month, it was considered poor adherence to the serving counter.

Participants were advised to attend the lectures and serving counter assessment sessions. After a discussion with participants, the dates and times for lectures and investigator visits were arranged to ensure maximum participation.

### Control

No intervention was implemented for the control clusters. However, they were asked not to refrain from attending any routine health education or promotion activities conducted by other health care institutions and persons.

### Outcome Measures

#### Overview

Postintervention assessment was conducted at the end of the intervention period in the same manner for the intervention and control clusters. The same data collectors who conducted the baseline (preintervention) data collection were recruited for the postintervention data collection. However, the study arm (intervention or control) to which an office belonged was not disclosed to the data collectors.

SOC data were collected using the same staging algorithm as in the baseline or preintervention data collection. The same 24-hour dietary recall with the picture guide and computer software were used to collect data on dietary intake at the postintervention assessment.

#### Primary Outcome

The primary outcome of the intervention was a progressive change in the SOC, which was defined as *progression from a lower SOC to a higher SOC*.

#### Secondary Outcome

The secondary outcome was a change from an unhealthy to a healthy diet or persistence in a healthy diet.

A healthy diet was defined as adherence to the recommended servings in the FBDG for Sri Lankans for more than 3 food groups, including cereal and cereal-based foods, fruits, and vegetables, with the consumption of 1 or no unhealthy foods per day. The recommended servings of different food groups per day are shown in Table 2.

**Table 2 table2:** Recommended number of servings of different food groups per day.

Food group	Number of servings
Rice, bread, other cereals, and yams	6-7 (6-11^a^)
Fruits	2-3
Vegetables	3-5
Milk or milk products	1-2
Fish, pulses (legumes), meat, and eggs	3-4
Nuts and oily seed	2-4

^a^Wider allowance was given to the rice, bread, other cereals, and yams food group in the Food-Based Dietary Guidelines as the energy requirements differ with activity level and sex. Because office workers were considered a sedentary group based on the nature of their duties, 6 to 7 servings of the rice, bread, other cereals, and yams food group were considered the recommended number of servings based on expert opinion.

The FBDG recommend variety in the food items consumed from each food group and in the number of servings specified in Table 2. However, the routine Sri Lankan dietary intake does not include all 6 food groups in daily meals. Therefore, we considered the 3 most consumed and important food groups (cereals, vegetables, and fruits) to be included in the definition of a healthy diet. In addition, we included a limit for unhealthy foods (foods containing only sugar and fat and highly processed foods) in the definition.

### Data Analysis

The distribution of basic sociodemographic characteristics, NCD status, dietary behaviors and practices, and work-related characteristics of the participants in the intervention and control arms will be assessed to determine whether the 2 groups were comparable at baseline.

Bivariate and multivariate analyses will be used to assess the effectiveness of the intervention. Progressive improvement in the SOC will be used as the primary outcome. Those who underwent a progressive change in their SOC will be coded as 1, and those who did not undergo such a change will be coded as 0. Similarly, those who changed from an unhealthy to a healthy diet or persisted in a healthy diet will be coded as 1, and those who did not will be coded as 0. Furthermore, changes in the intake of individual food groups to recommended levels will be coded as 1 and 0 similarly.

Bivariate analysis will use the primary and secondary outcomes as the dependent variables and sociodemographic factors, NCD status, dietary behaviors, and social relations as the independent variables. The chi-square test, independent-sample *t* test (2-tailed), and Mann-Whitney *U* test will be used as appropriate. Multivariate analysis will be conducted using binary logistic regression with the forward selection option to build the model. The variables included in the model will be determined based on demonstrating significant associations with the outcome variables in the bivariate analysis.

Sociodemographic factors, NCD status, dietary behaviors, social relations, and the allocated arm of the participants lost to follow-up will be compared with those of other participants to ensure no selective data loss. Further analysis will be conducted separately under two assumptions as follows: (1) all participants lost to follow-up achieved the primary and secondary outcomes, and (2) all participants lost to follow-up did not achieve the primary and secondary outcomes.

Odds ratios will be reported for the 2 assumptions separately. The level of probability will be set at .05 for all analyses.

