## Introduction

### Background

An unhealthy diet, which can be defined as nutritionally of poor quality or harmful to health [1], has a significant and well-established impact on developing noncommunicable diseases (NCDs) and their complications. It was highlighted that an unhealthy diet accounted for 11 million deaths and 225 million disability-adjusted life years in 2017 [2]. The Food-Based Dietary Guidelines (FBDG) for Sri Lankans provide directions on the necessary amount of food intake and dietary practices for a healthy diet [3]. The FBDG for Sri Lankans have 12 recommendations for a healthy diet, including the amount of food to be consumed [4]. The NCD risk factor survey (STEPS survey) conducted in 2015 highlighted that nearly 75% of male and female individuals were not consuming the recommended amount of fruits and vegetables [5]. An unhealthy diet is common among the workforce, and office workers are at higher risk of developing NCDs due to their sedentary lifestyle at work [6]. Studies conducted in the local context have also highlighted the increased prevalence of unhealthy diets among office workers [7,8]. Because working adults spend most of their time at the workplace, and due to the clustering of common risk factors and behaviors in one place, workplace-based interventions are believed to be successful. Several local and global studies have shown the effectiveness of interventions in workplaces [9,10].

Behavior change does not occur randomly, and behavior change theories explain the mechanism of behavior change [11]. The stage of change (SOC) theory describes 5 stages through which individuals can go through in changing their behavior, and it also describes interventions needed to be conducted at each stage to bring about the behavior change [12]. SOC theory is known to be effective in changing physical activity and dietary behavior, smoking and opioid addiction cessation, and dental hygiene improvement [13], whereas stage-matched interventions have been more successful and effective [14-16].

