The first question was “Do you follow healthy dietary guidelines?” If the answer was “yes,” the participant was asked, “for how long have you practiced your current diet?” (response options: “more than 6 months” [maintenance stage] and “less than 6 months” [action stage]). If the answer was “no,” the participant was asked, “are you seriously thinking of changing to a healthy diet in the next 6 months?” If the answer to the latter was “yes,” the participant was asked, “are you going to change your dietary habits next month?” If the answer was “yes,” the participant was allocated to the preparation stage. If the answer was “no,” the participant was allocated to the contemplation stage. If the answer to the question “are you seriously thinking of changing to a healthy diet in the next 6 months?” was “no,” the participant was allocated to the precontemplation stage.

To minimize bias due to misperception of the diet’s healthiness, the initial question was modified to read the following: “Have you changed your diet by reducing the amount of carbohydrates, salt, and sugar and increasing the amount of fruit and vegetable portions?”

The SOC of a participant was determined by coupling the staging algorithm with dietary assessment as suggested by Greene et al [28]. The perceived SOC reported by the participants was amalgamated with their dietary intake. Participants who followed a diet that met the definition of a healthy diet were assigned to their perceived SOC as reported by them. For example, if a participant reported being in the action or maintenance stages and their diet met the overall definition of a healthy diet, they were allocated to their reported SOC. In contrast, if participants who followed a diet that did not meet the definition of healthy dietary intake reported being in the action or maintenance stage, they were allocated to the preparation stage. This approach is summarized in Table 1.

**Table 1 table1:** Summary of the process of ascertaining the stage of change of the participants.

Staging algorithm result	Type of diet based on 24-h recall	
	Healthy	Unhealthy
Precontemplation	Precontemplation	Precontemplation
Contemplation	Contemplation	Contemplation
Preparation	Preparation	Preparation
Action	Action	Preparation
Maintenance	Maintenance	Preparation

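### Participants already at Maintenance at baseline can only be coded as failures on the primary outcome, and baseline stage is not listed for the model

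*Protocol article*

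**What the plan says.** The Primary Outcome section defines success as "progression from a lower SOC to a higher SOC". The Data Analysis section turns this into a binary variable: "Those who underwent a progressive change in their SOC will be coded as 1, and those who did not undergo such a change" are coded 0.

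The Background section says the theory "describes 5 stages through which individuals can go through in changing their behavior". In the staging algorithm and Table 1 (Data Collection), Maintenance is the last of them. Action and Maintenance are told apart only by duration: "response options: “more than 6 months” [maintenance stage] and “less than 6 months” [action stage". A dietary check is added. Participants whose recall is not healthy but who "reported being in the action or maintenance stage, they were allocated to the preparation stage".

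The eligibility criteria exclude nobody by stage, and the Intervention section describes a serving counter and app for the Preparation, Action and Maintenance stages. The Secondary Outcome section, by contrast, credits staying well: "The secondary outcome was a change from an unhealthy to a healthy diet or persistence in a healthy diet".

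The independent variables listed in Data Analysis are sociodemographic factors, NCD status, dietary behaviors and social relations. The final model is built by forward selection from those significant in bivariate tests. Participant Timeline names stage of change as a baseline item separate from dietary practices and intake, so it is not plainly covered by that list.

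**The concern.** A baseline Maintenance participant has no higher stage to move to. The coding gives the same 0 to someone who keeps a healthy diet throughout and to someone who relapses, in both arms. That person can be a success on the secondary outcome and must be a failure on the primary one. The first loss-to-follow-up scenario, in which everyone lost is assumed to have achieved the primary outcome, assigns such a participant a result that cannot occur.

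A share of zeros that no intervention can change shrinks the difference between arms and costs power. Baseline stage is then a very strong predictor of the outcome. Leaving it out, or leaving it to forward selection, means that a chance difference in stage mix between 10 and 10 offices goes uncorrected.

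A smaller, related issue concerns Action. Two Action participants who both keep a healthy diet can receive different codes because of how long each had been on the diet at baseline.

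**Working it through.** **Logic of the coding**

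| Baseline stage | Best possible result at follow-up | Code |
|---|---|---|
| Precontemplation, Contemplation, Preparation | a higher stage | 1 |
| Action, healthy diet kept, 6 months passed | Maintenance | 1 |
| Action, healthy diet kept, 6 months not passed | Action | 0 |
| Maintenance, healthy diet kept | Maintenance | 0 |
| Maintenance, diet lost | a lower stage | 0 |

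Nothing in the eligibility, outcome or analysis sections changes the last two rows. For Action, follow-up is at 3 months. At that interval, only participants already about 3 months into the diet at baseline can cross the 6-month line. The calendar in Participant Timeline (2 months of baseline collection, 1 month of roll-out, 3 months of intervention) could stretch the gap to about 6 months for some offices.

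**The plan's own sample size**

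With 0.30 v 0.45, two-sided 5% and 80% power:
- n = (1.96 + 0.84)² × (0.30×0.70 + 0.45×0.55) / 0.15² = 7.84 × 0.4575 / 0.0225 = 159.4, so 160 per arm.
- Design effect = 1 + (30 − 1) × 0.02 = 1.58, and 160 × 1.58 = 252.8, so 253.
- 253 / 0.9 = 281, close to the stated 280.

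The figure reproduces. It rests on fruit and vegetable intake, so it makes no allowance for participants whose stage outcome is fixed.

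**Illustration of the Maintenance effect**

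Inputs from the article: 439 participants at follow-up, so 219.5 per arm on average; 10 offices per arm; ICC 0.02; 0.30 v 0.45. Assumed: a share q at Maintenance in each arm, and 0.30 v 0.45 progressing among all others.

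- Mean cluster size is 219.5 / 10 = 21.95, so the design effect is 1 + 20.95 × 0.02 = 1.419.
- Rates with everyone included: p₁ = 0.30(1 − q), p₂ = 0.45(1 − q).
- SE = √{[p₁(1 − p₁) + p₂(1 − p₂)] × 1.419 / 219.5}.
- Power comes from the noncentral t with 18 df (20 offices minus 2), with noncentrality (p₂ − p₁)/SE.
- If Maintenance participants are excluded, the rates return to 0.30 v 0.45, with n and cluster size both multiplied by (1 − q).

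At q = 0: SE = √(0.4575 × 1.419 / 219.5) = 0.0544, noncentrality 0.15 / 0.0544 = 2.76, power 74%.

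| q | Rates, all included | Difference (points) | Power, all included | Power, Maintenance excluded |
|---|---|---|---|---|
| 0% | 0.300 v 0.450 | 15.0 | 74% | 74% |
| 2% | 0.294 v 0.441 | 14.7 | 73% | 74% |
| 5% | 0.285 v 0.4275 | 14.25 | 71% | 73% |
| 10% | 0.270 v 0.405 | 13.5 | 67% | 71% |
| 20% | 0.240 v 0.360 | 12.0 | 59% | 67% |

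**Chance imbalance at the upper share**

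At q = 20%, the SE of the difference in Maintenance share between arms is √(2 × 0.16 × 1.42 / 219.5) = 4.5 points, a 95% range of about ±9 points. Each point moves the outcome difference by the average progression rate, (0.30 + 0.45)/2 = 0.375. So 9 points shifts it by 0.09 × 0.375 = 3.4 points.

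**What the article says about shares**

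The Figure 2 legend splits the 266 intervention participants into 143 and 123 by stage, without saying in the legend which group is which. Preparation, Action and Maintenance together are therefore 54% or 46%. Because that group includes Preparation, this bounds the Maintenance share only loosely.

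**The case against.** The strongest objection is that the shares may be small. Maintenance requires a recall meeting a strict definition: cereals at 6-7 servings, fruit and vegetables at recommended levels, more than 3 food groups met, and at most one unhealthy food. The sample-size section cites only 28% of the population meeting fruit and vegetable servings alone. At 2-5% in Maintenance, the loss is about 1 to 4 power points and exclusion recovers about 1 to 2. This stands, and it is why the range above starts at 2%. The 30% v 45% is also not a rate of stage progression, so every power figure is illustrative.

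A second objection is that an outcome named progression may deliberately leave persistence to the secondary outcome. That is a legitimate choice of endpoint. It does not explain why people who cannot progress stay in the denominator as failures.

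A third is that chance imbalance under randomisation is random error, not bias. This is correct. The case for adjustment is precision and protection against an unlucky draw.

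A reader might infer that Action participants become successes simply because time passes, so that those successes say nothing about the intervention. The documents do not support this. Table 1 requires the follow-up recall still to be healthy; otherwise the participant falls to Preparation and is coded 0. The intervention for these stages is meant to support behavior already started, so it could influence that persistence. Those not far enough into the diet at baseline cannot cross. Modelling an equal crossing rate in both arms would assume the absence of effect that it then reports as dilution.

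**Conclusion.** The point holds for Maintenance. As written, the primary code of every baseline Maintenance participant is 0 in both arms, and no section of the article removes or credits them. Baseline stage is not among the listed model variables, and even if offered it would depend on forward selection.

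The consequence is dilution and lost power, not a systematic false-positive result. Its size is unknown: power of 73-59% against 74% for an assumed 2-20% in Maintenance, under the borrowed 30% v 45%, ICC 0.02 and equal shares in both arms. It may be near the small end.

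The Action issue is secondary. The code depends partly on time already spent on the diet, but a success still requires a healthy diet at follow-up and so can partly reflect the intervention. It justifies a sensitivity analysis and no more.

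**What to change.** Declare the following before the effectiveness analysis is run:

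1. Restrict the primary denominator to participants below Maintenance at baseline. Stage was recorded before randomisation, so the randomised comparison is kept. Report Maintenance participants separately by arm, as stayed or relapsed. Apply the same denominator to the two loss-to-follow-up scenarios.
2. Put baseline stage into the primary model as a fixed factor, not subject to forward selection. This belongs with step 1: with Maintenance participants included, a term for a category in which every outcome is 0 has no finite maximum-likelihood estimate.
3. As a sensitivity analysis, restrict to participants below Action at baseline. Recoding Action-to-Maintenance as no change is not a good alternative, because every Action participant would then become a structural zero.
4. Report the baseline stage distribution by arm, so that readers can see how much the restriction matters.

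No new data are needed, since baseline stage is already recorded. The cost is a slightly smaller denominator and a change to the primary analysis set made after data collection. The report should state it openly as such, with its date relative to the analysis, and give the result under the published coding alongside it.

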### Participant Timeline

Data from a cross-sectional study were extracted for all selected government offices in the Galle district, and 2 months were allocated for this. Data on participants’ demographic profiles, health conditions, dietary practices, SOC, and dietary intake were extracted from the aforementioned cross-sectional study as preintervention or baseline data for the interventional study. Randomization was conducted following the baseline data collection. Once randomization was done, the principal investigator and resource person for lectures visited each office in the intervention arm on a prescheduled day. All participants in the study were informed of the date beforehand. The principal investigator applied the intervention, and the resource person delivered lectures. If any participant missed the initial intervention, a second visit was arranged to achieve maximum participation. The initiation of the intervention in all 10 selected offices was completed within 1 month. Monthly assessments and lectures were conducted on prescheduled days following one, two and three months of the initiation date for each office. However, a second day was not arranged for monthly assessments and lectures. A postintervention assessment was conducted at the end of 3 months. The date for the postintervention evaluation was given to all participants to ensure that they took part in the assessment. If any participant missed the postintervention assessment, another day was arranged. Figure 1 shows the flow of participants through the intervention process.

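### Baseline stage of change is not a guaranteed covariate in the primary model, although the outcome is measured from it; baseline diet is at most a candidate that selection can drop

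*Protocol article*

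**What the plan says.** All references are to the protocol article.

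- **Data Analysis, covariates.** The bivariate step takes "sociodemographic factors, NCD status, dietary behaviors, and social relations as the independent variables".
- **Data Analysis, entry rule.** The model is a binary logistic regression built by forward selection: "The variables included in the model will be determined based on demonstrating significant associations with the outcome variables in the bivariate analysis". No covariate is exempt.
- **Participant Timeline.** Stage and diet were both available before randomization: "dietary practices, SOC, and dietary intake were extracted from the aforementioned cross-sectional study as preintervention or baseline data".
- **Primary Outcome.** The endpoint is "progression from a lower SOC to a higher SOC", coded 1 or 0.
- **Secondary Outcome.** The endpoint is "a change from an unhealthy to a healthy diet or persistence in a healthy diet". The coding rule is that "those who changed from an unhealthy to a healthy diet or persisted in a healthy diet will be coded as 1".
- **Data Collection and Table 1.** Baseline diet also enters staging. Participants with an unhealthy diet who "reported being in the action or maintenance stage, they were allocated to the preparation stage".
- **Intervention.** Lectures go to the two lowest stages, and the serving counter goes to the other three.
- **Randomization.** Twenty numbered offices were divided into two sets of 10 by a sequence generator. No stratification or matching is described.

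Baseline SOC is also not named in the baseline comparability check or in the comparison of participants lost to follow-up.

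**The concern.** A participant's chance of scoring 1 on the primary outcome depends on the starting stage, partly by construction:

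- Someone in maintenance has no higher stage and must score 0.
- Someone in action can reach maintenance as time passes, because the boundary is 6 months on the current diet and follow-up is 3 months.
- Someone in precontemplation or contemplation can move up to preparation on self-report alone, while preparation to action also requires a diet that meets the healthy definition on recall.

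The variable most closely tied to the primary outcome is therefore absent from the stated list. Even if it were added as a candidate, the entry rule would not guarantee that it stays. With 10 offices per arm and no stratification described, the two arms can differ in stage mix by chance, and part of any such difference passes into the estimated effect. The precision that adjustment would bring is also given up.

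**Working it through.** **The plan's own figures.** The article gives no figure for covariate adjustment. Its sample size reproduces: (1.96 + 0.84)² × (0.30×0.70 + 0.45×0.55) / 0.15² = 159.4, so 160 per arm. The design effect is 1 + 29×0.02 = 1.58, and 160 × 1.58 = 252.8, so 253. These figures do not bear on the point, except that they supply the intraclass correlation (ICC) of 0.02 borrowed below.

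**Inputs from the article.** Recruited: 266 intervention and 252 control (Results), 518 over 20 offices, mean 25.9 per office. Intervention-arm split by stage group: 143 and 123 (Figure 2 caption), so w = 143/266 = 0.538. Which stage group is which is not stated, but w(1−w) = 0.2486 either way.

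**Assumptions.** The ICC of baseline stage is 0.02, with a range of 0.01 to 0.05. The progression gap between the two stage groups is 20 to 40 percentage points. The article gives neither.

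**Step 1: chance imbalance in stage mix.** SD = √[w(1−w) × DE × (1/266 + 1/252)], with DE = 1 + 24.9×ICC.

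- ICC 0.02: DE = 1.498, and SD = √(0.2486 × 1.498 × 0.007728) = 0.054. The 95% range is about ±10.5 points. The chance of more than 5 points is 35%, and of more than 10 points about 6%.
- ICC 0.01: SD = 0.049. ICC 0.05: SD = 0.066.

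**Step 2: effect on the unadjusted difference.** Shift = imbalance × progression gap. For a 1-SD imbalance at ICC 0.02:

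- gap 20 points: 0.054 × 20 = 1.1 points
- gap 30 points: 0.054 × 30 = 1.6 points
- gap 40 points: 0.054 × 40 = 2.1 points

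A 10-point imbalance would give 2 to 4 points, but it lies 10/5.4 = 1.85 SDs out.

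**Step 3: precision.** An office-level simulation was run (20 offices, 22 analysed in each, 3,000 runs per setting, true effect 15 points). It compared arms without adjustment and after adjustment for a two-level stage group. Power at stage ICC 0.02 and 0.05:

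- progression 40% v 20%: 80% and 79% unadjusted; 82% and 82% adjusted
- progression 45% v 15%: 79% and 76% unadjusted; 84% and 83% adjusted
- progression 50% v 10%: 78% and 74% unadjusted; 86% and 86% adjusted

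Type I error was about 5% with and without adjustment. The SD of the estimate fell from 0.050–0.053 to 0.046–0.049. The 15-point effect is borrowed from the fruit-and-vegetable assumption in Sample Size, so these powers illustrate the gain and do not predict this trial's power.

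**Step 4: the secondary coding.** There are four possible paths. Unhealthy to healthy scores 1, healthy to healthy scores 1, healthy to unhealthy scores 0, and unhealthy to unhealthy scores 0. The code equals healthy at follow-up whatever the baseline. Baseline diet is therefore an expected predictor of this outcome and not a component of it.

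**The case against.** **The list may not be closed.** It names broad categories and does not even name the arm, so it may be condensed wording. The dietary-behaviors category could be read to include baseline diet, perhaps even stage. This stands for baseline diet, whose exclusion is not proven. It is weaker for SOC, because Participant Timeline lists it as an item of its own: "health conditions, dietary practices, SOC, and dietary intake were extracted". Under either reading, the stated entry rule leaves any such variable as a candidate only.

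**Not adjusting is not an error.** This stands. Chance imbalance is ordinary sampling error, and type I error in the simulation is the same either way. Choosing offices with similar work and size may also reduce imbalance somewhat.

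**Stronger readings a reader might infer.**

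- *The estimates are biased, or healthy-at-baseline participants are wrongly credited to an arm.* The documents do not support this. Randomization balances these participants in expectation, and healthy diet at follow-up is a legitimate endpoint.
- *A large spurious effect is likely, measured against the 15-point target.* That target belongs to fruit and vegetable intake, not to SOC progression, and the stage-specific progression rates are assumed.
- *Dropout by stage has already biased the comparison.* In the intervention arm the two groups fell from 143 to 127 and from 123 to 97, losses of 11% and 21%. No control-arm split is given, so bias between arms cannot be inferred. The end counts also sum to 224, against 220 in Results, so the rates are approximate.

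**A fully categorical SOC term causes trouble.** This stands too. Every maintenance-stage participant scores 0, so the logistic model has quasi-complete separation at that level and no finite coefficient for it. The remedy has to deal with this.

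**Conclusion.** The point holds as a matter of efficiency and robustness, not of validity. The article states a covariate list and an entry rule. Together they leave out the baseline variable from which the primary outcome is measured, and they make adjustment for baseline diet depend on the data.

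On the assumed inputs, chance imbalance in stage mix has an SD of about 5 points (4.9 to 6.6 for ICC 0.01 to 0.05). At ICC 0.02 it moves the progression difference by about 1 to 2 points per SD. In the illustrative settings, adjustment adds roughly 2 to 12 points of power. The size rests on the assumed stage ICC and progression gap and would shrink if stages progress at similar rates. The case is firm for baseline SOC and the primary outcome, and softer for baseline diet and the secondary outcome. A fuller analysis plan, not seen here, may already force baseline SOC. If so, only the article's description needs reconciling with it.

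**What to change.** 1. **Primary model.** Include baseline ascertained SOC with arm as a prespecified covariate, exempt from screening and forward selection. Either group the stages (for example precontemplation and contemplation versus preparation and above, which matches the two intervention packages), or keep finer stages with a prespecified method for the maintenance level, such as a penalized fit. A sensitivity analysis among participants able to progress is another way to deal with that level.
2. **Secondary model.** Force in baseline healthy-diet status, and describe the outcome as healthy diet at follow-up adjusted for baseline.
3. **Food-group models.** Force in baseline adequacy of the same food group.
4. **Timing.** The article says the effectiveness analysis was still to be completed. Date this choice before outcomes are examined by arm.

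**Cost.** No new data are needed. The cost is small but not nil: the reported odds ratio becomes conditional on baseline and will differ from the unadjusted one even without imbalance, and sparse stage levels need a stated rule. Reporting the unadjusted result alongside would let readers see both.
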